## **6. Other baseline variables**

- xxvi. Age (numerical data)
- xxvii. Laterality of ocular inflammation (categorical data): unilateral or bilateral
- xxviii. Sex (categorical data): male or female
- xxix. Onset (numerical data): days of ocular complaints
- xxx. Chronicity (categorical data): acute or chronic
- xxxi. Previous TB (categorical data): yes or no
- xxxii. Contact TB history (categorical data): yes or no
- xxxiii. Baseline visual acuity (numerical data): Snellen/LogMAR visual acuity, and categorical data: mild visual impairment, moderate visual impairment, severe visual impairment, and blindness.
- xxxiv. IOP (numerical and categorical data): increased or not
- xxxv. Keratic precipitates (categorical data): mutton-fat, fine, or others
- xxxvi. Anterior chamber cells (numerical data)
- xxxvii. The presence of iris nodule (categorical data): yes or no
- xxxviii. Scleral involvement (categorical data): yes or no
- xxxix. Synechia formation (categorical data): yes or no
  - xl. Lens status (categorical data): cataract, pseudophakia, phakic)
  - xli. Vitreous haziness (categorical data): yes or no
  - xl.ii. Vitreous cells (numerical data)
  - xl.iii. Snowball/snowbank (categorical data): yes or no
  - xliv. Retinal vascular changes (categorical data): yes or no
  - xl. v. Optic nerve involvement (categorical data): yes or no
  - xlvi. Retinitis or retinal infiltrates (categorical data): yes or no
  - xl. vii. Choroiditis (categorical data): yes or no
  - xl. viii. Posterior granuloma/tuberculoma appearance (categorical data): yes or no
  - xl. ix. Retinal detachment (categorical data): yes or no
    - l. Macular edema (categorical data): yes or no

## **7. Sample size calculation**

The sample size is calculated using a formula of two-independent proportion sample size calculation. The primary end point of uveitis resolution at 6 month is used for this sample size calculation.

Based on the Multicenter Uveitis Steroid Treatment (MUST) trial in non-infectious uveitis, the proportion of uveitis patients with active disease at six months following treatment was found to be 44%. A 30% difference in uveitis resolution between the two groups is predetermined. Using a  $Z\alpha$  of 1.96 and a  $Z\beta$  of 0.84 (for a two-sided significance level of 5% and 80% power), the estimated sample size required for each treatment group will be 35 participants. With 10% increase to anticipate dropout, a total of 39-40 participants in each treatment group is required.

$$N1 = N2 = \left( \frac{Z\alpha\sqrt{2PQ} + Z\beta\sqrt{P1Q1 + P2Q2}}{P1 - P2} \right)^2$$

$Z\alpha$  (1.96), power (80%,  $Z\beta = 0.84$ ),  $P1$  based on MUST trial 44% ( $Q2 = 56\%$ ). Estimated  $P1 - P2 = 30\%$ . Thus,  $P2 = 14\%$  ( $Q2 = 86\%$ ). As 10% drop out rate is being anticipated,  $N1 = N2 = 39 \sim 40$  (total 78-80 participants)

## 8. Randomization

After eligibility assessment, participants will be randomly assigned in a 1:1 ratio to one of the two treatment groups without stratification factors. Randomization will be performed by a dedicated research manager/assistant using block randomization (block size of 4) to ensure equal distribution between the groups.

(Note: Patients presenting with choroidal granuloma or serpiginous-like choroiditis will be directly assigned to the ATT group, in accordance with recently published guidelines coinciding with the start of this trial. Adjustments to the randomization will be made afterwards to maintain the block size)

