**Study design & study population:****Single blind randomized controlled trial (RCT) – single center**

All newly referred uveitis patients will be evaluated for eligibility at the outpatient uveitis clinic, Department of Ophthalmology, Faculty of Medicine, Universitas Indonesia - Cipto Mangunkusumo Hospital, Jakarta, Indonesia.

Inclusion criteria are: (1) adults (age  $\geq 18$  years) with newly diagnosed, clinically active uveitis of undetermined cause, following standardized workups at our center (see Supplementary file); (2) positive QFT test result ( $>0.35$  U/mL; Kimia Farma Laboratory, Depok, PT. Kimia Farma Diagnostika); (3) local residence in Jakarta, Bogor, Depok, Tangerang, or Bekasi; and (4) consent to participate in the study through the entire monitoring period. Exclusion criteria were: (1) confirmed active systemic TB or living with an active TB patient; (2) HIV-positive status; (3) visual acuity less than hand movement with signs of phthisis on ophthalmological examinations and ultrasound; (4) impaired liver function or other systemic conditions, as assessed by the internist-pulmonologist, that precluded eligibility for ATT; (5) pregnancy, and (6) recent antibiotic use, including ATT, or systemic steroid use exceeding 8 mg prednisone equivalent daily within the last 14 days.

Ocular PCR will be performed in selected cases based on the clinical judgement of the attending uveitis specialist. This will be done (1) to confirm the clinical diagnosis, or (2) to exclude other differential diagnosis. If it is performed, any positive results will result in exclusion from trial entry.

After eligibility assessment, participants will be randomly assigned in a 1:1 ratio to one of the two treatment groups without stratification factors. Randomization will be conducted by a dedicated research manager using block randomization (block size of 4) to ensure equal distribution between the groups.

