## 9. Study analysis population

### c. The intention-to-treat (ITT) approach

All analyses will be first conducted using the ITT approach. The ITT population will include all participants who underwent randomization, regardless of any treatment switching that occurred. For participants who missed the six-month visit ( $\pm 28$  days), if any, last observation carried forward (LOCF) imputation will be performed..

d. The per-protocol approach

The per-protocol population will include all participants who were randomized, excluding those who do not have six-month visits or deviated from the treatment protocols (e.g., non-compliant, experience severe adverse effect, etc). If any, participants who switch treatment will also be excluded in this per-protocol analysis.

For patients receiving ATT, missing 2 weeks of medication will be considered non-compliance (protocol deviation). The pulmonologist will record the prescribed ATT and count the remaining drugs (i.e., ATT) at each visit to determine treatment non-compliance. For participants receiving systemic immunosuppressants, missing more than 1 week of the prescribed regimen will be considered non-compliance. Topical immunosuppressants will not be taken into account when determining compliance.

e. Additional approach for potential switching

In order to anticipate treatment switch, adjustment will be performed, particularly to analyze the secondary outcomes. Participants grouping will be subdivided into those receiving combination treatment besides the initial group of ATT alone and non-ATT. Specifically, participants that switch from non-ATT group to ATT will be classified as ATT in this adjusted analysis. Analysis following adjustment for switching treatment was performed with recalculation of the six-month follow-up time based on the actual treatment received, beginning from the start of their actual treatment.

However, results from the ITT analysis (without adjustment for switching) is considered to be more appropriate to evaluate the primary outcome, given that the purpose of the study was to compare the two strategies according to the treatment received at the time of randomization.

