## **14. Data analysis**

- a. All data will be pseudo-anonymized. A separate dataset (in Excel) containing participant IDs will be protected. A separate dataset without direct participant IDs will be generated and analyzed using SPSS.
- b. Baseline characteristics will be summarized according to trial group for the ITT populations.
- c. The primary outcome analysis will be focused on the proportion of complete uveitis resolution and the corresponding relative risk between the ATT and control groups. Cox proportional-hazards models will be used to estimate any uveitis resolution between the ATT and control groups. This analysis will be performed at the patient level, where resolution of uveitis is considered when both eyes meet the prespecified criteria. In bilateral

uveitis cases, if one eye shows uveitis resolution but the other does not, as prespecified in the previous section, these participants will be considered to have “no uveitis resolution”.

- d. Pairwise comparisons across experimental arms will be done using a Chi-square test or Fisher’s exact test as appropriate at the 5% significance level for the efficacy endpoint of uveitis resolution at six month time point (see above section). Relative risk will be calculated and presented with 95% confidence interval in the ITT and per-protocol analysis approaches.
- e. Time-to-uveitis resolution will be analyzed using the Cox proportional hazards model and hazard ratio.
- f. For uveitis relapse outcomes, the analysis will include participants with complete uveitis resolution, regardless of follow-up duration. Cox proportional hazards models, along with hazard ratio and Kaplan–Meier estimates, will be used for the analysis.
- g. The number (proportion) of participants experiencing any adverse events will be reported.
- h. Eye-level outcomes will be calculated based on the involved eyes for the presenting uveitis. Therefore, bilateral uveitis presentations will be counted as two eyes.
- i. A *p*-value of less than 0.05 will be considered statistically significant.
- j. All statistical analyses will be performed using IBM SPSS Statistics version 28.0.1.0 (142) for Windows (SPSS Inc.).

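### Two lesion phenotypes enter the ATT group without randomisation, and the SAP does not say whether they count in the randomised comparison or how the block list is adjusted for them

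*Supplement*

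**What the plan says.** The final protocol (v2.0, Protocol Summary, study design) states: "After eligibility assessment, participants will be randomly assigned in a 1:1 ratio to one of the two treatment groups without stratification factors". It gives no exception by lesion type. Neither eligibility list in that protocol (the summary or section 3) excludes choroidal granuloma or serpiginous-like choroiditis.

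SAP v2.0 section 8 opens with the same 1:1 scheme, "using block randomization (block size of 4) to ensure equal distribution between the groups". A note in the same section then says "Patients presenting with choroidal granuloma or serpiginous-like choroiditis will be directly assigned to the ATT group" and continues: "Adjustments to the randomization will be made afterwards to maintain the block size". The method of adjustment is not described.

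SAP section 9c defines the main analysis set: "The ITT population will include all participants who underwent randomization, regardless of any treatment switching that occurred". The per-protocol set in 9d also starts from randomised participants. Neither definition mentions the directly assigned patients.

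SAP section 14c states: "The primary outcome analysis will be focused on the proportion of complete uveitis resolution and the corresponding relative risk between the ATT and control groups". Section 14 also adds Cox models for resolution and relapse. No model term or exclusion for lesion type is specified. Section 6 lists choroiditis and posterior granuloma as baseline variables only.

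**The concern.** By rule, these two phenotypes can occur only in the ATT arm. If they are in the comparison, lesion and treatment cannot be separated. Adjustment does not help, because no directly comparable control exists. The protocol's own introduction warns that letting severity at presentation influence the decision to give ATT complicates the interpretation of its benefit; this note lets assignment by presentation back in.

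Two analysts could follow this SAP in good faith and report different primary results, one counting these patients in the ATT group and the other dropping them as never randomised. The second choice costs power if they occupied ATT places, and the sample size makes no allowance for that.

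Blinding is also affected. According to the treatment table, a blinded attending uveitis specialist decides on immunosuppressants, and steroid dose is part of the primary endpoint. A specialist who sees the lesion and knows the rule knows that patient's arm.

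**Working it through.** **1. The plan's own sample size (SAP section 7).** Inputs: active disease at six months P1 = 0.44, P2 = 0.14, mean P = 0.29, Zα = 1.96, Zβ = 0.84.

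n = [(1.96·√(2·0.29·0.71) + 0.84·√(0.44·0.56 + 0.14·0.86)) / 0.30]² = [(1.258 + 0.509)/0.30]² = 34.67, so 35 per arm. 35/0.9 = 38.9, so 39. The stated 35 and 39-40 reproduce. The calculation assumes that everyone is randomised 1:1.

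**2. The texts side by side.**

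| Text | Are directly assigned patients in the comparison? |
|---|---|
| Protocol v2.0 summary | The case does not arise; participants are randomised |
| SAP 8, note | They are in the ATT group, and the list is adjusted afterwards, which implies that they count |
| SAP 9c and 9d, read literally | No; they were never randomised |
| SAP 11 (safety) | Yes; enrolled, exposed participants, by treatment regimen |
| SAP 14f (relapse) | Participants with complete resolution; no randomised-only limit of its own |

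No text resolves the conflict.

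**3. If they are counted.** Let m be the number directly assigned among 40 ATT patients and g the gap between their resolution probability and that of the other ATT patients. Both are assumptions, since the documents give neither.

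Bias in the risk difference = (m/40) × g.
- m = 4, g = 0.20: 4/40 × 0.20 = 0.02.
- m = 8, g = 0.40: 8/40 × 0.40 = 0.08.

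That is 2 to 8 points against a planned difference of 30, in either direction.

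For the effect on error rates, take 40 per arm, 56% resolved in non-lesion patients in both arms (no ATT effect), and an assumed resolution rate of 26% to 86% in lesion patients:
- m = 4: expected difference −3 to +3 points; two-sided type I error up to 5.8%.
- m = 8: −6 to +6 points; up to 8.4%. For example, at 86% the ATT rate is (32·0.56 + 8·0.86)/40 = 0.62 against 0.56.

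With a true 30-point effect in non-lesion patients (86% v 56%) and m = 8, power runs from 39% when the lesion rate is 26% to 86% when it is 86%.

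**4. If they take ATT places and are then left out.** Assume 40 controls, 40 − m randomised ATT patients, 10% dropout in both arms, and resolution of 86% v 56%.

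Power = Φ[(0.30 − 1.96·se0)/se1], with se0 = √[p̄(1−p̄)(1/nA + 1/nC)] and se1 = √[0.86·0.14/nA + 0.56·0.44/nC].

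| m | nA | nC | se0 | se1 | Power |
|---|---|---|---|---|---|
| 0 | 36 | 36 | – | – | 81.5% |
| 4 | 32.4 | 36 | 0.1108 | 0.1028 | 79.0% |
| 8 | 28.8 | 36 | 0.1153 | 0.1050 | 76.0% |

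Without dropout the figures are 85.5%, 83.3% and 80.5%. The plan's target is set "for a two-sided significance level of 5% and 80% power".

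**The case against.** The best counter-argument is that the ITT and per-protocol definitions already solve the problem: patients never randomised fall outside both, the SAP runs all analyses first by ITT, and baseline characteristics are summarised for the ITT population. On that literal reading no confounding reaches the primary relative risk. This stands as far as it goes, and it makes the bias conditional. It does not close the matter. The SAP never says these patients are excluded, it names them as part of the ATT group, and adjusting the randomisation on their account makes little sense if they do not count.

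A reader might infer several stronger things that the documents do not support:

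- That the two arms are not randomised groups at all. The note can add non-randomised patients only to the ATT arm; every control and every other ATT patient is still randomised.
- That each direct assignment uses up an ATT slot. This is a strong inference from the wording about block size, but the method is not described, and the slot could instead be replaced.
- That the note creates predictable allocation. A 2/3 chance of control after one ATT allocation in a block, and certainty after two, are ordinary properties of any 2:2 block of four. What the note adds is that a clinician who recognises the lesion knows that one allocation. Exploiting it would also require knowing the position in the block, and a research manager or assistant runs the list.
- That the bias is known to be large. The number of such patients could be zero; with 4 of 40, type I error in the illustration reaches only 5.8%.

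**Conclusion.** The concern holds in this limited form. SAP section 8 conflicts with its own opening sentence, with the final protocol and with the ITT definition, and the plan settles neither how directly assigned patients are analysed nor how the list is changed on their account. Counting them confounds the primary relative risk and the Cox models by phenotype. Dropping them after they have filled ATT places takes power with 10% dropout from 81.5% to about 79% (4 patients) or 76% (8 patients).

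The bias of 2 to 8 points rests wholly on assumed numbers and an assumed prognosis gap, and its direction is unknown. The power figures rest on assumed numbers and on the inference that ATT places are consumed. The problem is not irreparable: limiting the comparison to randomised patients removes these patients from it. It should be settled before analysis because the validity of the primary comparison depends on it. No view is taken on which treatment these patients should receive.

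**What to change.** Reconcile the protocol's randomisation paragraph with SAP sections 8 and 9, as follows:

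1. State in both documents that patients with these lesions are not randomised, take no slot in the list and cause no change to it. Delete the sentence on adjusting the randomisation.
2. Restrict the primary, per-protocol, time-to-resolution, relapse and eye-level comparisons, and the 78-80 count, to randomised patients.
3. Report directly assigned patients descriptively as a separate cohort, with their safety data shown separately.
4. If any have already been placed, make randomised patients only the primary analysis, and report how many there were and what was done to the list.

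The cost is a wording change in the SAP and protocol. Recruitment takes slightly longer or the randomised sample is slightly smaller, and the conclusion does not extend to these two phenotypes. Nobody's treatment changes.

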## 9. Study analysis population

### c. The intention-to-treat (ITT) approach

All analyses will be first conducted using the ITT approach. The ITT population will include all participants who underwent randomization, regardless of any treatment switching that occurred. For participants who missed the six-month visit ( $\pm 28$  days), if any, last observation carried forward (LOCF) imputation will be performed..

d. The per-protocol approach

The per-protocol population will include all participants who were randomized, excluding those who do not have six-month visits or deviated from the treatment protocols (e.g., non-compliant, experience severe adverse effect, etc). If any, participants who switch treatment will also be excluded in this per-protocol analysis.

For patients receiving ATT, missing 2 weeks of medication will be considered non-compliance (protocol deviation). The pulmonologist will record the prescribed ATT and count the remaining drugs (i.e., ATT) at each visit to determine treatment non-compliance. For participants receiving systemic immunosuppressants, missing more than 1 week of the prescribed regimen will be considered non-compliance. Topical immunosuppressants will not be taken into account when determining compliance.

e. Additional approach for potential switching

In order to anticipate treatment switch, adjustment will be performed, particularly to analyze the secondary outcomes. Participants grouping will be subdivided into those receiving combination treatment besides the initial group of ATT alone and non-ATT. Specifically, participants that switch from non-ATT group to ATT will be classified as ATT in this adjusted analysis. Analysis following adjustment for switching treatment was performed with recalculation of the six-month follow-up time based on the actual treatment received, beginning from the start of their actual treatment.

However, results from the ITT analysis (without adjustment for switching) is considered to be more appropriate to evaluate the primary outcome, given that the purpose of the study was to compare the two strategies according to the treatment received at the time of randomization.

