## 10. Study follow-up

Participants will be assessed at screening, baseline (Week 0), Week 2, and then at monthly intervals until the primary endpoint at 6 months (Month 1, Month 2, Month 3, Month 4, Month 5, and Month 6). If deemed necessary by the attending uveitis specialist or pulmonologist, visits outside this schedule will be possible while preserving blinding. The research manager will continue contacting participants for subsequent monthly visits beyond the primary endpoint at 6 months, though these visits are not mandatory. If a scheduled visit does not occur or if its results are missing, the value measured on the date closest to the target scheduled visit within a

window period of  $\pm 2$  weeks will be used. If the latest visit does not fall within the 6-month period ( $\pm 2$  weeks), the closest visit to this timeframe will be used.

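### Two unranked rules fix the primary outcome when the six-month visit is missed, and the LOCF rule can bias the comparison if loss to follow-up differs by arm

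*Supplement*

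**What the plan says.** - **SAP v2.0 section 9c (ITT approach), repeated in protocol v2.0 section 6.** All randomised participants are analysed. If the six-month visit is missed, with a window of 28 days either side, "last observation carried forward (LOCF) imputation will be performed".
- **SAP v2.0 section 10 (Study follow-up).** Visits are monthly to Month 6 and optional afterwards. The window is two weeks either side. If the latest visit lies outside it, "the closest visit to this timeframe will be used". The text does not restrict this to earlier visits.
- **SAP v2.0 section 7 (Sample size).** The control arm is assumed to have 44% still active at Month 6, taken from an outside trial, and ATT is assumed to do 30 points better. At two-sided 5% and 80% power this leads to 35 per arm. On losses the section adds: "With 10% increase to anticipate dropout, a total of 39-40 participants in each treatment group is required".
- **SAP v2.0 section 14.** The primary test is chi-square or Fisher's exact at 5%. Relative risks are reported for the ITT and per-protocol sets. The per-protocol set omits participants without a six-month visit.

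No other analysis addresses missing primary outcomes.

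**The concern.** Two sections of the same SAP define the primary-endpoint value for the same situation, with different windows and different fallbacks. With no order of precedence, the analyst has to choose, and could do so after outcomes are known.

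LOCF also fits this endpoint poorly. Uveitis must be active at entry, and resolution needs both quiet eyes and a daily oral dose of at most 7.5 mg prednisone. Someone lost early, with active disease or still on a higher dose, is scored as not resolved whatever happened later. Someone lost after resolving keeps a success. The score therefore partly measures when a person left. Carrying one value forward also treats a guess as an observation, which understates uncertainty.

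The trial has about 40 per arm, so a few participants matter. The planned rates correspond to roughly 22 of 40 resolved on control and 34 of 40 on ATT (uncorrected chi-square p = 0.003). Changing four ATT participants to failures gives 22 v 30 and p = 0.061.

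**Working it through.** **1. The plan's own figure.** Inputs from SAP section 7: P1 = 0.44, P2 = 0.14, Z values 1.96 and 0.84. The mean P is 0.29, so 2PQ = 2 × 0.29 × 0.71 = 0.4118, and P1Q1 + P2Q2 = 0.2464 + 0.1204 = 0.3668.

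n = [(1.96 × √0.4118 + 0.84 × √0.3668) / 0.30]² = 34.67, rounded up to 35. Then 35 / 0.9 = 38.9, so 39. The stated 35 and 39–40 are reproduced.

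**2. The two rules side by side.**

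| Attendance | Section 9c | Section 10 | Same record? |
|---|---|---|---|
| Last seen Month 4, never again | Month 4 | Month 4 | Yes |
| One visit three weeks off Month 6, none nearer | That visit (inside 28 days) | That visit (outside two weeks, but closest) | Yes |
| Month 4, then Month 7.5 | Month 4 | Month 7.5 (1.5 months away, against 2) | No |

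The rules part when no visit falls within 28 days and a later, optional visit is nearer than the last earlier one.

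**3. Model for LOCF.** Let p be an arm's true six-month resolution rate (0.56 control, 0.86 ATT, from section 7), d the share lost, and f the fraction of p that those lost had reached at their last visit. The scored rate is p(1 − d) + p·f·d. The documents do not give f or any split of loss by arm. Both are assumptions, shown over a range. Power is exact for the two-sided uncorrected chi-square test at 40 per arm.

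**4. Equal loss of 10%, as planned.**

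| f | Control | ATT | Difference (points) | Power |
|---|---|---|---|---|
| 0 (all carried as failures) | 50.4% | 77.4% | 27.0 | 72% |
| 0.5 | 53.2% | 81.7% | 28.5 | 79% |
| 0.6 | 53.8% | 82.6% | 28.8 | 80% |
| 1 (no dilution) | 56.0% | 86.0% | 30.0 | 86% |

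A separate assumption, that those lost have the same outcome in both arms (44% to 100% failure), fixes the difference at 0.9 × 30 = 27 points and gives 71–76% at 39–40 per arm.

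**5. Unequal loss, true effect 30 points.**

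| Assumed loss | f | Difference (points) | Power |
|---|---|---|---|
| 15% ATT, 5% control | 0 | 73.1 − 53.2 = 19.9 | 46% |
| 15% ATT, 5% control | 0.5 | 79.55 − 54.6 = 24.95 | 67% |
| 5% ATT, 15% control | 0 | 81.7 − 47.6 = 34.1 | 91% |
| 10% each | ATT 0, control 0.8 | 77.4 − 54.9 = 22.5 | 57% |
| 10% each | ATT 0.8, control 0 | 84.3 − 50.4 = 33.9 | 91% |

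**6. No true effect (56% in both arms), 15% ATT and 5% control loss.** With f = 0 the scored rates are 0.56 × 0.85 = 47.6% and 0.56 × 0.95 = 53.2%. The spurious difference is 5.6 points against ATT, and the test rejects 8.8% of the time. With f = 0.5 it is 2.8 points and 6.4%. With equal 10% loss the rejection rate is 5.6–5.7%.

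**The case against.** **The conflict touches few people.** This stands. For anyone who never returns, both rules select the same visit. Only late returners are affected, and their number cannot be known beforehand.

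**Power.** A reader might infer that LOCF defeats the 10% inflation and costs the trial its 80% power. The documents do not support that. LOCF keeps all 40 per arm, which starts at 86% and leaves a cushion. The 71–76% range requires no treatment effect at all among those lost. The dilution is also not peculiar to LOCF: scoring every missing participant as not resolved gives the same 72%.

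**Source of bias.** A reader might infer that participants who stop ATT for adverse events are scored as failures while controls who feel well and leave are scored as successes. Stopping ATT is not loss to follow-up: under ITT with monthly visits, someone who stops but attends is scored on real data. Nothing in the documents shows why controls would leave. An early leaver need not be on a steroid taper either, since immunosuppressants in the ATT arm are only possible, not required.

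**Success after loss.** The protocol summary itself counts resolution with too little later follow-up as maintained, so this direction of scoring does not come from LOCF alone. That is correct.

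**Existing check.** The per-protocol analysis drops participants without a six-month visit. It gives some comparison, but it also removes switchers and non-compliers, so it does not isolate missing data.

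**Conclusion.** The point holds in two parts. First, the final SAP gives two unranked rules and two windows for the primary-endpoint value, and they select different visits for some late returners. Second, LOCF makes the score depend on departure time, so it biases the comparison if loss to follow-up differs by arm in rate or timing. The direction cannot be known in advance. Step 6 shows a possible size, 5.6 points and 8.8% rejection under no effect, but the 15%/5% split and the carried failures are assumptions.

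The sample size has no arithmetic error. Under the planned 10% equal loss, power runs from 72% to 86%, reaching 80% once those lost had attained about 60% of their arm's resolution rate. It is fair to say that 80% is not guaranteed, but not that it is lost. The leverage of four missing participants per arm applies to any way of handling them. It is a reason to fix the rule in advance, not evidence against LOCF in particular.

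**What to change.** - State one window and one rule identically in SAP 9c, SAP 10 and protocol section 6. For example: nearest visit within 28 days either side of Month 6, otherwise missing.
- Say how that rule works with the protocol summary's provision for resolution followed by too little follow-up, which the change above leaves in place.
- Replace LOCF by multiple imputation using arm, the Month 1–5 inflammation grades and steroid dose, and a small set of baseline values. Keep the model parsimonious: with 36 observed on ATT and 14% failing, only about 36 × 0.14 = 5 failures are expected there.
- Prespecify two sensitivity analyses: missing counted as not resolved, and a tipping-point table that varies the assumed outcome separately by arm.

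The cost is SAP and protocol wording, some analysis work, slightly wider intervals, and an imputation model that must stay simple at this sample size. No new visits or data are needed. The change will not by itself raise power.
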